### Randomisation

When the participants have returned the questionnaire and they fulfil all inclusion criteria and none of the exclusion criteria, they are randomised. The investigator contacts the Copenhagen Trial Unit (CTU) by telephone, and the CTU staff will perform the allocation according to data entered in a computer system. Participants will be randomised individually 1:1 to the experimental group versus the control group centrally according to a computer-generated allocation sequence with a varying block size concealed to investigators. Randomisation will be stratified according to age (up to 39 years, or older than 40 years); self-reported hand eczema severity (‘none and light’ or ‘moderate, severe, and very severe’); and profession (‘healthcare’, ‘kitchen or cleaning staff’, ‘hairdresser or construction worker’, or ‘all other professions’). After the allocation, the investigators will inform the participants about the allocation by telephone.

### Blinding

It is not possible to blind the participants or investigators with respect to treatment allocation. However, data entry from the questionnaires, outcome assessment regarding absence from the work force (the eight week follow-up telephone calls, data from the DREAM register, and data from other national registers), statistical analyses, and conclusions will all be blinded.

### Trial duration

The inclusion period is estimated to be 18 months. The first participant was included in 13 July 2012, and we expect inclusion of the last participant in December 2013. Self-reported data on absence from work will be continuously collected (every eighth week). Follow-up for the individual participants will be 12 months after inclusion and is expected to be completed in December 2014.

### Experimental group

The experimental intervention consists of four components, A to D, as well as usual care, E:

A. *Group education on general skin-protective behaviour*

Participants in the experimental group will participate in a two-hour course. One or two courses per week will be available. A secretary or nurse will arrange booking with the participants allocated to the experimental group. A maximum of 12 participants per course is expected. The courses will be conducted by two investigators. Participants can choose between an evening and a daytime course.

The group education will comprise basic knowledge about the skin, the development of eczema, and recommendations for skin protection and care. The recommended skin protection programme has been summarized into ten recommendations in Denmark (Table 1). These ten recommendations will be the basis of the education [27].

There will be practical demonstrations in hand washing and use of disinfectants, use of moisturiser, and use of different types of gloves (cotton, rubber, nitrile, vinyl gloves, and gloves with and without fingers).

B. *Job-specific counselling on work-related skin-protective behaviour, which might extend to a work-place visit*

The job-specific counselling will comprise specific recommendations for skin care in different occupations. For ten occupations with some of the highest numbers of recognised occupational hand eczema patients in 2010 [28], the information will be standardised and written information will be available (Table 2). In case of other occupations, or with specific problems, a work visit will be offered and arranged. A doctor or a nurse will undertake the visit, and counselling will be based on this.

C. *Social guidance related to occupational hand eczema*

The social guidance related to the occupational hand eczema will include information on rules and rights during an occupational injury. This will also include information about the options for help from workers compensation or social welfare in case of job-loss or change.

D. *Telephone hotline*

An occupational nurse will provide assistance via telephone about questions and social problems. The telephone hotline will mainly include information already given at the course, but may be more specifically given to the particular individual. The purpose of the hotline is to repeat information from the course, which may have been forgotten or misunderstood, and to guide the participant in case of questions related to the social situation related to the occupational skin disease. It is the intention that the hotline shall generally function as a ‘helping hand’.

E. *Treatment and care as usual*

The experimental group will have access to usual treatment and care (see below).

**Table 1 T1:** **The ten recommendations regarding how to avoid hand eczema**[27]

1.	Use gloves when beginning wet work tasks.
2.	Gloves must be used as long time as necessary but as short as possible.
3.	Protective gloves should be intact and clean and dry inside.
4.	When protective gloves are used for more than 10 minutes, cotton gloves should be worn underneath.
5.	Wash hands in lukewarm water and dry them well.
6.	Alcohol-based disinfections should be used instead of soap when the hands are not visibly dirty.
7.	Do not wear rings at work.
8.	Use a moisturiser with a high fat content and no perfume.
9.	Moisturisers should be applied all over the hands, including the webs, finger tips and dorsal aspects.
10.	Take care also when doing domestic work. Use protective gloves for dish washing and insulating gloves in the winter.

**Table 2 T2:** **Ten occupations where job-specific recommendations for skin care is available**[28]

**Occupation**	**Number of recognised occupational hand eczema patients in 2010**
Health care workers, care workers not hospital	456
Kitchen workers/chef, baker, butcher	214
Cleaners	118
Craftsmen	105
Hairdresser	101
Factory worker	88
Mechanics, machine operator, metal worker	113
Sales assistant	41
Dentist assistant	39
Gardener, agricultural worker	37

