### Control group

The control group will not have access to the components A to D encompassing group education, the profession specific information, the social guidance, and the telephone hotline, but they have access to usual treatment and care with their general practitioner and dermatologist (component E).

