#### Participation in the experimental intervention

Participation in the course will be registered in paper record forms by the investigators and later manually registered in SAS.

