### Plan for statistical analyses

#### Analysis of the three primary outcomes

##### Types of analyses

Depending on the specific type of outcome measure, one of three types of regression analyses will be applied.

• *Type 1* includes a rate (count of events over period of observation (12 months according to plan). Using the countreg procedure (SAS 9.3), the Poisson model, and the negative binomial model, the rate will be compared by testing for overdispersion and comparing the average predicted count probabilities and the observed proportions. The best model will be used to analyse data.

• *Type 2* includes a continuous outcome measure. The general linear univariate model will be used.

• *Type 3* The ordinal outcomes will be analysed using the proportional odds model where the intervention group indicator is included as a co-variate provided the P value of the score test of the proportional odds assumption is ≥ 0.05.

All of the above analyses will include the three protocol specified stratification variables (age groups, self-reported hand eczema severity, and profession) as covariates in addition to the intervention indicator and baseline value if available. If the assumptions of an analysis are seriously violated, a non-parametric test will be used.

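### Only the experimental arm is taught in groups, but the sample size and primary models treat all participants as independent; if courses themselves differ in effect, the planned standard errors are modestly too small

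*Protocol article*

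**What the plan says.** The Randomisation section of the protocol article makes the individual the unit: "Participants will be randomised individually 1:1 to the experimental group versus the control group". The Experimental group section then describes a two-hour course, booked after allocation, with a choice of daytime or evening: "One or two courses per week will be available", and "A maximum of 12 participants per course is expected. The courses will be conducted by two investigators". The Control group section confirms that the other arm has no such grouping: "The control group will not have access to the components A to D encompassing group education".

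The Sample size estimation section takes the largest of three calculations, 742 in total (371 per arm), at a type I error of 1.67% and 80% power. No allowance for course appears there. The Types of analyses section fixes a Poisson or negative binomial model, a general linear model and a proportional odds model, and gives their terms: "All of the above analyses will include the three protocol specified stratification variables", plus the intervention indicator and the baseline value where there is one. No course term, random effect or robust variance is named. The only mixed model, under Exploratory analyses, is for repeated sick-leave rates over time.

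Attendance is already captured: "Participation in the course will be registered in paper record forms by the investigators", with later entry into SAS.

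**The concern.** This is an individually randomised trial with group treatment in one arm (a partially nested design). People who share a session share its teaching, demonstrations and discussion. If some sessions work better than others, outcomes within a course are correlated, and the experimental-arm mean is less precise than an independent-observation formula says. Standard errors are then too small, and the 1.67% used in planning and the 5% familywise limit are exceeded. Hommel's adjustment does not cure this, because it controls the familywise rate only when the P values fed into it are valid.

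The article does not leave this open. It names the model types, their covariates and the sample size formulas, all on the basis of independence.

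**Working it through.** **Inputs from the protocol article.** 371 per arm; difference 5 days, SD 21; type I error 0.05/3; power 80%; one or two courses a week; at most 12 per course; "The inclusion period is estimated to be 18 months". **Assumption:** ICC 0.01 to 0.05, since none is given.

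**1. The plan's own figures.** With z = 2.394 (two-sided 1.67%) and 0.842 (80% power), n per arm = 2 × (2.394 + 0.842)² × (SD/difference)².
- Sick days: 2 × 10.47 × (21/5)² gives 370 per arm, 740 in total (stated 742).
- DLQI: 2 × 10.47 × (4.8/1.2)² gives 336 per arm, 672 in total (stated 672).
- Severity, 60% against 48%: the two-proportion formula without continuity correction gives 360 per arm, 720 in total (stated 720).

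All three come from independent-observation formulas, so no clustering allowance is hidden in them.

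**2. Course size.** 18 months is about 78 weeks, so 78 to 156 courses. 371/78 = 4.8 and 371/156 = 2.4 per course. Twelve is the ceiling.

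**3. Variance inflation.** In the experimental arm the design effect is DE = 1 + (m − 1) × ICC; in the control arm it is 1. The variance of the difference is inflated by V = (1 + DE)/2. For example, at m = 12 and ICC 0.05: DE = 1.55 and V = 1.275.

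**4. Error rate and power.** This treats sick days as a mean, with equal course sizes and a normal approximation.
- Actual error of the planned test: 2 × (1 − Φ(2.394/√V)).
- Standardised effect: 5/(21 × √(2/371)) = 3.243.
- Power of the planned test: Φ((3.243 − 2.394)/√V).
- Power of a test that allows for course: Φ(3.243/√V − 2.394).

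| Mean course size | ICC | Nominal 1.67% becomes | A single nominal 5% test becomes | Power, planned test | Power, allowing for course |
|---|---|---|---|---|---|
| 2.4 | 0.01 | 1.70% | 5.1% | 80.1% | 79.9% |
| 2.4 | 0.05 | 1.86% | 5.4% | 79.8% | 78.7% |
| 4.8 | 0.01 | 1.77% | 5.2% | 80.0% | 79.4% |
| 4.8 | 0.05 | 2.21% | 6.1% | 79.1% | 76.0% |
| 12 | 0.01 | 1.98% | 5.6% | 79.6% | 77.7% |
| 12 | 0.05 | 3.40% | 8.3% | 77.4% | 68.4% |

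Keeping 80% power while allowing for course would need 744 to 810 participants at sizes 2.4 to 4.8, and 780 to 942 at size 12.

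**5. Where the correlation comes from.** The formulas assume that the course itself creates the correlation. Simulation under no average effect separates two cases.
- Courses differ in effect, ICC 0.05: the planned 1.67% test rejects about 2.2% of the time at size 4 and 3.4 to 3.8% at size 12, in line with the table.
- Similar people merely book the same slot: the planned test stays at about 1.6 to 1.9%, even with strong sorting. A cluster-robust test becomes conservative, rejecting under 0.1% of the time with courses of 12 and an ICC of 0.25.

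**The case against.** Several objections stand and limit the point.

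- **Not every correlation matters.** A reader might infer that any likeness within a course inflates the error, including likeness from choosing evening or daytime. It does not. Slots are booked after individual randomisation, so the experimental-arm mean is still that of a random sample and the ordinary standard error holds.
- **No direction.** A reader might infer that the plan tilts towards declaring the course effective. An understated standard error biases neither the estimate nor its sign; false findings of harm become more frequent to the same degree.
- **Power.** A reader might attach the 68 to 78% or 76 to 80% to the plan as written. Those figures belong to a test that allows for course. The planned test loses about one point at the implied course sizes and under three at the ceiling.
- **Size.** Twelve is a maximum. Non-attendance makes courses smaller, and the content is built on ten fixed recommendations and standardised job information, which may keep the ICC low. The article does not say that leaders differ between courses.
- **Blinding.** A course identifier exists in one arm only, so adding it to the data reveals allocation, while the Blinding section requires blinded analyses and conclusions.

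It can also be said that a variance option belongs in the analysis plan, which is not shown. That carries less weight, because the article fixes models, covariates and sample size without any course term, and an analysis plan that followed it would inherit the omission.

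**Conclusion.** The point holds conditionally and is modest in size. With any positive ICC produced by the courses themselves, the planned standard errors are too small. At the course sizes the schedule implies, a nominal 1.67% test runs at about 1.7 to 2.2%; it reaches 2.0 to 3.4% only if courses run at the ceiling of 12. This rests on the assumed ICC of 0.01 to 0.05, on all 371 attending, and on equal course sizes; unequal sizes would raise the design effect somewhat. The documents do not support a claim of serious inflation, of bias in favour of the course, or of a large loss of power in the planned test. The change is still worth making, because it is cheap and puts an estimated ICC in place of an untested assumption.

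**What to change.** 1. Add a course identifier to the existing attendance form and carry it into the analysis data.
2. Fit each primary model with a random course effect in the experimental arm only. Alternatively, use a cluster-robust variance with each course as a cluster and each control and each non-attender as a cluster of one. Report the ICC for each outcome.
3. Protect the blinding. Either give controls sham course codes of similar size (with a similar share of singletons, and a separate course variance for each coded arm), or prespecify the course-adjusted analysis to be run after the blinded conclusions have been drawn.
4. In the sample size section, state the assumed ICC and mean course size. Beside the 80%, give the power of the analysis that allows for course: about 76 to 80% at sizes 2.4 to 4.8, and 68 to 78% at 12.

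The cost is one data field, a change to the model or variance specification, and the coding step for blinding. Intervals become slightly wider, and the test is conservative if the clustering comes only from who chose which slot.

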### Control group

The control group will not have access to the components A to D encompassing group education, the profession specific information, the social guidance, and the telephone hotline, but they have access to usual treatment and care with their general practitioner and dermatologist (component E).

### Usual treatment and care available to both intervention groups

After notification to the National Board of Industrial Injuries, a medical examination including allergy testing of the patient will take place. This will be either as a specialist’s certificate performed by a specialist in dermatology, or an examination in a dermatological department in a hospital. The decision to recognise or reject the patient as having an occupational disease will be based on data from this investigation.

The participants in both intervention groups have access to the usual care and treatment with the general practitioner and dermatologist. Such care will be registered via central registers.

### Concomitant medication and treatment

All medication and other treatment are permitted during the trial. We will register use of topical corticosteroids and visits with a dermatologist for all participants in the follow-up period.

### Data collection

#### Inclusion

Participants fill in a questionnaire regarding basic demographic factors, self-reported level of eczema severity using a photographic guide [29], health-related quality of life (the Dermatology Life Quality Index) [30], level of knowledge concerning prevention of hand eczema, occupational exposure and exposure during leisure time, strength of coping, and performance management. The questionnaires are returned by mail. Data will be entered into Statistical Analysis Software (SAS). This will be done by scanning and where that is not possibly, manually, by external assistants.

#### Participation in the experimental intervention

Participation in the course will be registered in paper record forms by the investigators and later manually registered in SAS.

#### Follow-up period, from inclusion to 12 months after inclusion

Data on absence from workforce will be collected every eight weeks, by telephone call, e-mail, text message or any other chosen form of media by a blinded investigator, for one year in the intervention group and in the control group. The data will be registered directly in paper record forms by a nurse. Absence will be categorised by participants as: total sick leave; eczema-related sick leave; absence from work for other reasons (child care during illness, etc.); unemployment; and other reasons. Later these data will be entered into SAS by the external assistants.

#### End of follow-up, 12 months after inclusion

Participants fill in a follow-up questionnaire regarding self-reported level of eczema severity using a photographic guide [29], health-related quality of life (the Dermatology Life Quality Index) [30], level of knowledge concerning prevention of hand eczema, occupational exposure and performance management. The follow-up questionnaire will be distributed by mail to all participants and when returned, entered into SAS by scanning and where that is not possibly, manually, by external assistants. Data on absence from the work force for a period longer than 28 days will be collected from the DREAM register [31]. Further, data regarding potential effect modifiers, i.e., the participants’ use of topical corticosteroids will be collected from The Danish National Database of Reimbursed Prescriptions [32], and visits with a dermatologist will be retrieved from The National Health Insurance Service Registry [33]. Data from both national registers will be collected using the unique Danish Civil Registration Number.

### Data management

Data is handled and recorded in paper record forms and kept in records marked with investigator number, patient identification number, and name of region. The data on absence from work are handled and recorded in participant record forms and kept in records marked with investigator number, patient identification number, name of region, and time of assessment. Paper questionnaires collected at follow up (12 months) is kept in other records marked with investigator number, name of region, and time of assessment. After follow up all the record forms from each participant will be collected in individual files and kept in records. Any change in the files or participant record forms will be documented with date and signature of the investigator.

Data from the records will be registered electronically in SAS for statistical analyses. This will be done partly by scanning and partly manually by external assistants. Records will be archived for at least five years after end of trial.

### Quality control and quality assurance

To ensure the trial is conducted and reported in compliance with this protocol, the data are monitored internally. The investigators monitor the data and check for systematic errors. All data are registered in paper record forms and kept at an investigator site file available only for the investigators. Around 5% of the data is monitored to assess consistency between the paper record forms, electronically registered data, and signed consent forms. Data are handled with confidentiality.

### Primary outcomes

The PREVEX trial has three co-primary outcomes:

• **Total sick leave**; measured as self-reported total number of days with sick leave during the trial period.

• **Health-related quality of life;** measured as points scored in the Dermatology Life Quality Index (DLQI) at 12 months after inclusion [30].

• **Subjective assessment of hand eczema severity**; measured by use of a photographic guide at 12 months after inclusion [29].

### Explorative outcomes

The following outcomes will be assessed as explorative, as there is insufficient information to conduct power calculations.

• **Eczema-related sick leave;** measured as self-reported total number of days with eczema-related sick leave during the trial period.

• **Absence registered by the DREAM-register**; only absence for more than 28 days from workplace is registered here. This will be done at 12 months after randomisation. We will measure absence from work because of sick leave for more than 28 days, yes or no.

• **Absence, self-reported** total number of days with absence during the trial period.

• **Behaviour** measured as number of points achieved in a questionnaire concerning both occupational and private risk behaviour at 12 months after randomisation.

• **Knowledge of skin protection** measured as numbers of points achieved in a multiple choice questionnaire at 12 months after randomisation.

• **Performance management** at 12 months after randomisation of the participant measured by the number of points achieved in:

O Self-efficacy [34]; and

O Self-evaluated ability to self-care.

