## Background

Occupational hand eczema is the most frequently recognised occupational disease in Denmark [1]. The incidence is approximately 0.32 per 1,000 persons in the total population [2], and the numbers are comparable in most of the industrialised world [3].

In 2011, the Danish National Board of Industrial Injuries recognised a total of 1,395 individuals with occupational skin diseases, and the large majority of these patients (> 90%) had occupational hand eczema.

Hand eczema affects mainly young people as 1/3 has onset of disease before the age of 20 years [2]. The lifetime prevalence is almost twice as high in women as it is in men [1]. This is mainly due to women’s higher exposure to wet work, occupationally as well as privately, which are well known risk factors [3]. Other aggravating factors are atopic dermatitis and contact allergy [1].

Hand eczema often takes a chronic course. A Swedish follow-up study reported active eczema 12 years after onset of disease in 72% of the sample of patients and found that 15% had been excluded from the work force [4]. In a Danish study, similar data were reported [5,6]. During a one-year period, 20% of patients with notified hand eczema had sick leave for more than five weeks due to skin disease, and 20% to 25% had loss of job (examined in the time span between notification and recognition). 57% had sick leave because of skin disease during the first year after notification. These data show that the burden of the disease is high in a personal as well as in a socio-economic context [7]. The number of persons with occupational hand eczema has remained unchanged despite public initiatives to reduce exposures to harmful allergens [8].

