### Participant withdrawal and discontinuation of participants

The participants are free to withdraw their informed consent from the trial at any time without effecting future treatment or their case processing in the National Board of Industrial Injuries. If a participant wishes to withdraw his or hers consent, they will be contacted and asked to specify which aspects of the trial they wish to withdraw from: participation in the experimental intervention, participation in follow-up interviews and answering the questionnaires, use of follow-up data collected from national databases, or complete withdrawal from trial, i.e., use of already collected data the analyses.

All participants who enter the trial will be accounted for in the publication of the results. Participants who fail in attending a course on a planned date will be contacted and offered a new course. Participants who cannot be reached during the follow-up period will be contacted and encouraged to resume contact. Participants who do not return the follow-up questionnaire will be contacted and a letter will be sent containing a questionnaire on reasons for drop out.

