##### Missing values

If the percent participants with missing values exceeds 5% for any of the three outcomes or Little’s test is significant (p < 0.05), multiple imputations (MI) will be used (SPSS version 17 or later).

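### DREAM long-term sick leave is not linked to missing co-primary sick leave, and the max/min sensitivity rule can assign totals that the register contradicts

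*Protocol article*

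**What the plan says.** All references are to the protocol article.

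- *Primary outcomes*: sick leave is "measured as self-reported total number of days with sick leave during the trial period". *Follow-up period* describes collection every eight weeks through the participant's chosen medium.
- *Participant withdrawal and discontinuation of participants*: a participant who withdraws is asked which parts to leave. The list names as separate items "participation in follow-up interviews and answering the questionnaires, use of follow-up data collected from national databases". Contact can therefore end while register follow-up continues.
- *End of follow-up*: "Data on absence from the work force for a period longer than 28 days will be collected from the DREAM register".
- *Explorative outcomes*: of DREAM, "only absence for more than 28 days from workplace is registered here", and the use made of it is "We will measure absence from work because of sick leave for more than 28 days, yes or no".
- *Missing values*: if more than 5% of participants have missing values for any co-primary, or Little's test is significant, "multiple imputations (MI) will be used (SPSS version 17 or later"). No predictors are named.
- *Sensitivity analyses*: gaps in one arm are filled with the largest observed value and gaps in the other with the smallest, then the arms are swapped. No exception is made for information held elsewhere.

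**The concern.** Being on long-term leave may itself lead people to stop answering. This is an assumption, but a plausible one. If so, the missing totals differ systematically from the observed ones, and multiple imputation is only as credible as the predictors that make missing-at-random reasonable. DREAM is an obvious candidate: it measures part of the same construct, does not depend on the participant replying, and is listed under *Blinding* as a blinded source. The article gives it no role here.

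The max/min rule raises a sharper issue because it is written down. It can assign the smallest observed total to a participant for whom the trial holds a record of more than 28 days' absence. In the reverse direction it can assign the largest total to someone with no registered long absence. What is at stake is how far the handling of missing data for a co-primary can be trusted.

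**Working it through.** **Yardstick.** The target difference for sick leave is 5 days with SD 21 (*Sample size estimation*). The SD reproduces: √9,786 × (7.15 − 6.32)/3.92 = 20.95. With α = 0.05/3 (two-sided assumed), 80% power and 1:1 allocation, n per group = 2(z₁₋α/₂ + z₀.₈₀)² × 21²/5² gives 370 (740 in total), and the t-based version gives 371 (742), the article's figure. The point does not affect that number. The 742 carries no stated allowance for missing data.

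**How much of the outcome may lie in long leave.** The *Background* reports an earlier study: "20% of patients with notified hand eczema had sick leave for more than five weeks due to skin disease". The expected mean here is about 20 days.

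- Lower bound on the contribution of those people: 0.20 × 35 = 7 days, and 7/20 = 35% of the mean, if the 20% carries over to this trial.
- Assumed gamma distribution with mean 20 and SD 21: about 25% of people exceed 28 days in the year and hold about 61% of all days. With an assumed SD of 40, the figures are 21% and 80%.

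These are yearly totals, not single spells, so they are upper guides to what DREAM would show. They describe where the days lie, not a bias.

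**What the max/min rule does.** With a fraction m missing in each arm, the rule adds m × (max − min) to the group difference. With an assumed maximum of 365 and minimum of 0:

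| m (assumed) | m × 365 | days |
|---|---|---|
| 5% | 0.05 × 365 | 18.25 |
| 10% | 0.10 × 365 | 36.5 |
| 20% | 0.20 × 365 | 73.0 |

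Each is several times the 5-day target.

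**What a register floor does.** Let q be the share of missing participants with a registered spell and d their registered days. The floor raises the mean of the arm given the minimum by m × q × (d − min). Take the least case: d just over 28, inside the follow-up year, and min = 0.

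- q = 0.20 (borrowed from the *Background*, an assumption): 0.05 × 0.20 × 28 = 0.28 days at 5% missing, and 0.20 × 0.20 × 28 = 1.12 days at 20%.
- q = 1 (every missing participant on long leave): 0.05 × 28 = 1.4 and 0.20 × 28 = 5.6 days.

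Longer spells raise these figures in proportion. In these least cases the floor narrows the range only slightly. What it achieves for certain is to remove values that the trial's own data contradict. A matching ceiling for people with no registered spell would not be valid, since several shorter absences can add up to more than 28 days.

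**What the text links.** No section connects DREAM to missing self-reported sick leave, and none rules the connection out.

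**The case against.** The strongest reply is that this is an improvement and not an error. Scoring one exploratory outcome as yes/no does not limit what is extracted or used elsewhere, and *End of follow-up* describes the DREAM collection more broadly. A reader might infer that the imputation is planned to ignore the register. The article does not support that: *Missing values* names no predictors of any kind, and the choice is commonly left to an analysis plan, which is not shown. This part of the reply stands, so for multiple imputation the point is a request to name the variable.

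The max/min analysis is meant to be extreme and is not the main estimate. That also stands, and is why the fix adds a version and does not replace the planned one. But the rule is fixed in writing, and a bound that includes values known to be false for particular people says less than it could.

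A floor mixes a register measure with self-report. This is fair, and is the reason for reporting agreement between the two.

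Someone who stops midway may still contribute observed time, because sick leave is analysed as a rate over the observation period. This stands and reduces the number affected, though the later weeks of such participants remain unobserved.

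The documents do not show that the extract holds spell length or timing. The civil registration number sentence in *End of follow-up* refers to both national registers directly after naming the prescription and health-insurance registers, so it should not be cited for DREAM. The fix must therefore work with the yes/no indicator alone if need be.

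**Conclusion.** The point holds as a low-cost improvement to the handling of missing data for one co-primary. It is not a contradiction or a wrong figure. Three things are established: register follow-up can outlast participant contact, the article gives DREAM sick leave only a binary exploratory role, and the max/min rule makes no exception for registered leave.

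Three stronger readings are tempting and not supported.

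- DREAM cannot recover the missing total, because it omits absences of 28 days or less.
- Nothing shows that most people who stop answering keep register follow-up. The point applies to those who have not refused it.
- The 35% share is not a size of bias. It combines an earlier study's yearly totals with an expected mean that the article itself gives only as approximate.

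The gain cannot be computed, as neither a missing rate nor a DREAM day distribution is given. The case rests on the assumptions that long leave carries a large share of the days and that it may be related to non-response.

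**What to change.** 1. Keep the yes/no DREAM outcome as planned.
2. Name DREAM sick leave as an auxiliary variable in the multiple imputation of total sick leave, together with arm, the stratification variables and the reported periods. Use duration and timing of spells over 28 days if the extract holds them, otherwise the yes/no indicator. Apply this to every randomised participant who has not refused register data.
3. Alongside the planned max/min analysis, add a version in which no imputed total falls below the register-documented sick-leave days within that participant's 12 months.
4. Report agreement between DREAM and self-report among responders, so that readers can judge how far one informs the other.

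The cost is analysis-plan wording and possibly more detail from a register collection already planned, with no new contacts or participants. It should be settled before unblinded analysis. The downside is that DREAM misses shorter absences and measures a slightly different quantity from self-report, so it supplements the co-primary measure and does not replace it.
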